# A multicenter phase III study comparing Simultaneous Integrated Boost (SIB) radiotherapy concurrent and consolidated with S-1 versus SIB alone in elderly patients with esophageal and esophagogastric cancer – the 3JECROG P-01 study protocol

**DOI:** 10.1186/s12885-019-5544-1

**Published:** 2019-04-29

**Keywords:** Esophageal cancer, Esophagogastric junction cancer, Elderly, Concurrent chemoradiotherapy, Definitive chemoradiotherapy, Consolidated chemotherapy, Simultaneous integrated boost, Intensity modulated radiotherapy, Randomized controlled trial, S-1, Comprehensive geriatric assessment

## Abstract

**Background:**

The importance of definitive radiotherapy for elderly patients with esophageal and esophagogastric-junction cancer is pronounced. However, little is known in terms of the best way to combine radiotherapy with other treatment options. This study aims to compare the efficiency of SIB radiotherapy alone with SIB radiotherapy concurrent and consolidated with S-1 for elderly patients. Comprehensive geriatric assessment is also incorporated in the procedure of treatment.

**Methods/design:**

The study is a two arm, open, randomized multicenter Phase III trial with patients over 70 years old with stage IIA-IVB (UICC 2002, IVB only with metastasis to supraclavicular or celiac lymph nodes) squamous cell carcinoma or adenocarcinoma of esophagus or gastroesophageal junction. A total of 300 patients will be randomized using a 1:1 allocation ratio stratified by disease stage and study site. Patients allocated to the SIB arm will receive definitive SIB radiotherapy (95%PTV/PGTV 50.4Gy/59.92Gy/28f) while those randomized to SIB + S-1 arm will receive definitive SIB radiotherapy concurrent and consolidated with S-1. The primary endpoint of the trial is 1-year overall survival. Secondary objectives include progression-free survival, recurrence-free survival (local-regional and distant), disease failure pattern, toxicity profile as well as quality of life. Besides, detailed radiotherapy protocol and quality assurance procedure have been incorporated into this trial.

**Discussion:**

The proportion of elderly patients in esophageal cancer is now growing, but there is a lack of evidence in term of treatment standard for this group of patients, which is what we aim to obtain through this prospective phase III study.

**Trial registration:**

clinicaltrials.gov
NCT02979691. Registered November 22, 2016.

## Background

Esophageal and esophagogastric-junction cancer (EC and EGJC) is the fourth most common cancer in China and elderly EC/EGJC patients accounts for approximately 30~40% of all cases. [1, 2]. The management of elderly patients with EC/EGJC is still challenging as their relative poor physical conditions impose great limitations on their treatment. Generally, they are considered ineligible for esophagectomy, the major component of treatment norm for patients with resectable EC/EGJC, because of the high rates of postoperative morbidity and mortality (especially those received preoperative chemoradiation) [3, 4]. A promising alternative without major toxicity is definitive chemoradiotherapy (dCRT), which is initially designed for patients with locally advanced EC/EGJC. However, the dual-drug intravenous chemotherapy regimen (fluorouracil/capecitabine + platinum drugs) recommended by National Comprehensive Cancer Network (NCCN) [5] and European Society for Medical Oncology (ESMO) [6] may bring severe acute and late toxic effects and poor compliance rate in elderly population. Thus, a modified dCRT regimen specific to the elderly is in great demand.

In this paper, we propose a prospective phase III clinical trial to improve dCRT regimen for elderly patients in three aspects: First, S-1, a single chemotherapeutic drug will be used instead of the conventional two-drug chemotherapy regimen to improve therapeutic effect while maintaining the rate of toxicities at a relatively low level. Secondly, SIB technique will be adopted to increase the dose of regions at high risk, while simultaneously reduce the dose of organs at risk (OAR). The adopted radiation dose pattern come from a prospective phase I/II trial previously conducted in our center [7]. Finally, the specialty of elderly population will be considered by integrating comprehensive geriatric assessment (CGA) into treatment procedure.

CGA, a multidisciplinary evaluation of the elderly, usually covers functional status, cognitive capacities, emotional status, comorbidities, nutritional status, social and environmental situations, and a possible geriatric syndrome. Over the past decade, the CGA has been proposed as a tool for managing elderly patients with cancer [8–14]. However, no study has ever attempted to incorporate CGA to the treatment of patients with EC/EGJC. 3JECROG P-01 trial is the first large-scale prospective phase III study to combine CGA with the treatment of elderly EC/EGJC patients to the best of our knowledge.

To summarize, this prospective, multi-center phase III clinical trial is initiated in the expectation of obtaining high-level type I evidence for the standard treatment of EC/EGJC among elderly patients.

## Methods/design

### Study design and objectives

This study is an open, multicenter Phase III clinical trial. Approximately 15 participating centers throughout China are involved. The technique of SIB is adopted in this study with a dose of 50.4Gy/2.14Gy/28f to planning target volume (PTV) and 59.92Gy/2.14Gy/28f to planning gross tumor volume (PGTV). S-1 is given both concurrent with and after radiotherapy. Patients enrolled are stratified by disease stage and study site and assigned to either SIB + S-1 group or SIB group using a 1:1 allocation ratio at randomization. A flow chart giving an overview of the study design is shown in Fig. 1.

**Fig. 1 Fig1:**
[figure not shown]
Flow chart of 3JECROG P-01

The primary objective of this trial is to compare the 1-year OS of SIB + S-1 group with SIB group. Secondary objectives include progression-free survival, recurrence-free survival (local-regional and distant), disease failure pattern, toxicity profile as well as quality of life.

The study started on February, 2017 and the duration of inclusion will be approximately 2 and a half years.

### Patient

#### Patient selection

Patients older than 70 years old with histocytologically proven stage IIA-IVB (UICC 2002, IVB only with metastasis to supraclavicular or celiac lymph nodes) inoperable squamous cell carcinoma (SCC) or adenocarcinoma (AC) of esophagus or gastroesophageal junction are eligible for recruitment. No other treatment is allowed before enrollment. For cancer of esophagogastric junction, the center of the tumor could not extend 2 cm into the gastric cardia. Patients must have adequate hematological, renal and hepatic functions defined as: neutrophils ≥3.5 × 10^9^/L, granulocytes ≥1.5 × 10^9^/L, platelets ≥100 × 10^9^/L, urea nitrogen (BUN) ≤ 1.0 × upper normal limit (UNL), creatinine (Cr) ≤ 1.0 × upper normal limit (UNL), alanine aminotransferase (ALT), aspartate aminotransferase (AST) ≤1.5× UNL; alkaline phosphatase (ALP) ≤ 1.5× UNL; total bilirubin ≤UNL. General condition of enrolled patients must be acceptable (i.e. Karnofsky Performance Status≥70 or Eastern Cooperative Oncology Group performance status ≤1, Charlson Comorbidity Index≤3).

Exclusion criteria include prior malignancies (other than curable non-melanoma skin cancer or in situ cervical cancer) within 5 years, distant lymph node (other than metastasis to supraclavicular or celiac lymph nodes) or visceral metastasis (including metastasis to bone, lung, liver, pleura or peritoneum, etc.), uncontrolled infection such as tuberculosis or hepatitis, uncontrolled hypertension or diabetes, severe comorbidities such as myocardial infarction, cerebral embolism or serious arrhythmia within 6 months, obvious sign of esophageal perforation or deep ulcer affirmed by barium esophagram.

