### Toxicity and adverse events

All treatment-related toxicities and adverse events should be graded according to the toxicity criteria of the Radiation Therapy Oncology Group (RTOG) and Common Terminology Criteria of Adverse Events (CTCAE) version 4.0 and recorded on patients’ case report form (CRF) in detail. Serious Adverse Events (SAE) should be reported to the institutional ethical review committee in 24 h and dealt with properly.

S-1 should be terminated in case of Grade 2 anemia, thrombocytopenia, hepatic or renal dysfunction, Grade 4 leukopenia/neutropenia, Grade 3 radiation esophagitis and other non-homological Grade 3 toxicities. If adverse events de-grade to Grade 0–1 within 1 week of drug withdrawal, patient can re-take S-1 at original dose, otherwise chemotherapy should be stopped henceforward. If Grade 3/4 radiation pneumonitis developed, both radiotherapy and oral intake of S-1 should be terminated. Consolidation of S-1 will be re-assessed within 4–8 weeks after radiotherapy whichever grade of toxicities developed during dCRT.

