### Statistical analysis & sample size considerations

We assume that an estimated difference in 1-y OS of 65% (SIB arm) versus 75% (SIB + S-1 arm) would justify applying this regimen in the future. Assuming a one-sided significance level of 0.05, a power of 0.80, and 10% of lost in each arm, a total of 300 patients would be needed in this trial.

Estimates of median OS will be based on the Kaplan-Meier method and log-rank tests will be used to determine the significance. Cox regression analysis will be conducted to identify prognostic factors for survival benefit, which will be used in adjusted analyses of the treatment effect.

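### The granulocyte entry limit is redundant beside the higher neutrophil limit, so one of the two lines is very probably mislabelled or carries the wrong value

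*Protocol article*

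**What the plan says.** The protocol article, under Patient selection, defines adequate organ function by a list of laboratory limits that every patient must meet. The list opens with "Patients must have adequate hematological, renal and hepatic functions defined as: neutrophils ≥3.5" × 10^9/L and continues directly with "granulocytes ≥1.5 × 10^9^/L, platelets ≥100 × 10^9^/L". The limits are listed jointly, with nothing to mark one as an alternative to another.

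The article defines neither term, does not explain why the two limits differ, and does not repeat or correct them elsewhere. The eligibility list contains no limit for total leukocytes. Under Toxicity and adverse events, in a rule on stopping S-1, the article refers to "Grade 4 leukopenia/neutropenia". There it names total white cells and neutrophils as separate, paired terms.

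**The concern.** Two different floors are set for overlapping cell counts, and the higher floor is placed on the narrower count. The granulocyte line therefore does no work. Authors rarely write a numeric entry criterion that cannot act, so an error of label or value in one of the lines is the likely explanation.

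The matter is more than editorial because these are binding entry limits. If the neutrophil line is printed as intended, the granulocyte line is superfluous. If the neutrophil line is the faulty one, the printed rule admits a different population from the one planned. A reader of the results would then misjudge to whom they apply, and the eligibility of a patient whose counts lie between the two limits could not be audited with confidence against this text.

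**Working it through.** No design figure (significance level, power, survival rates, sample size) enters this check. It concerns only the two limits.

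**Inputs**, both from the protocol article, Patient selection, in units of 10^9/L:
- neutrophils, N ≥ 3.5
- granulocytes, G ≥ 1.5

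**Step 1: relation between the counts.** Neutrophils are one class of granulocytes. Write O ≥ 0 for all other granulocytes. Then G = N + O, so G ≥ N.

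**Step 2: does the second limit ever act?** If N ≥ 3.5, then G ≥ N ≥ 3.5 > 1.5. Every patient who passes the neutrophil line passes the granulocyte line. The set of patients meeting both limits is the set meeting N ≥ 3.5 alone.

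**Step 3: numerical confirmation.** A grid with N from 0 to 10 and O from 0 to 2, each in steps of 0.1, was searched for combinations with N ≥ 3.5 and G < 1.5. It contained none.

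**Step 4: who is treated differently by the two lines?** Patients with N < 3.5 and G ≥ 1.5 fail the rule as printed but would be admitted by the granulocyte line alone. If other granulocytes are few, so that G is close to N (an assumption), this is the band 1.5 ≤ N < 3.5, which is 3.5 − 1.5 = 2.0 wide.

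**Step 5: how many patients is that?** The answer needs the distribution of baseline counts among screened patients. The article gives none, so the share cannot be computed.

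**Step 6: does other text resolve it?** The stopping rule for S-1 pairs leukopenia with neutropenia, while the eligibility list has no total leukocyte limit. That pattern would fit a mislabelled cell type. It does not establish one, and it does not show which line is wrong.

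**The case against.** The strongest reply has four parts.

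*The limits are compatible.* A reader might infer that the two lines contradict each other. They do not: a patient with N ≥ 3.5 satisfies both, and the rule as printed gives a definite answer for every patient. This stands. The defect is a redundancy, which makes an error very probable without proving it.

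*The consequences at the centres are not shown.* A reader might infer that some of the approximately 15 centres screen on one line and some on the other, that accrual slows, and that deviations cannot be resolved. The text supports none of this. Both limits are required, so nothing in it allows a centre to drop the neutrophil line. The article is also a condensed account. Recruitment began in February 2017 for about two and a half years, and the article appeared on 29 April 2019, roughly 26 of 30 months in. Centres must have been screening from other documents, which are not shown and may be worded differently. This also stands, and it decides what the first step of the fix should be.

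*The size is unknown.* A reader might infer that many patients are shut out. One can generate a figure: with a lognormal neutrophil count and log-SD 0.34, the share below 3.5 is Φ(ln(3.5/m)/0.34), which gives 43%, 35% and 23% for medians m of 3.7, 4.0 and 4.5. Neither the medians nor the spread come from the documents, and the result moves quickly with the median because those medians lie just above the cut-off. It shows sensitivity to assumption and is not an estimate for this trial.

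*The treatment comparison is protected.* Allocation is 1:1 and stratified by study site. An entry criterion applied before randomisation, even if applied unevenly between centres, affects both arms alike. This stands.

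None of the four makes the granulocyte line effective, and none points to text that corrects it. Nor is this a detail left to a fuller document: the article prints specific limits, and as printed they do not form a sensible pair.

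**Conclusion.** The point holds as a redundancy in a binding entry rule. The granulocyte limit can never exclude a patient who meets the neutrophil limit, and very probably one of the two lines names the wrong cell count or carries the wrong value. Read literally, the rule excludes patients with neutrophils below 3.5 × 10^9/L whom the other line alone would admit.

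The number of such patients is unknown and cannot be derived from the article. The effect is on the enrolled population and on the reach of the result; validity of the comparison between arms is not threatened. Different practice between centres and slower accrual are possibilities that the documents do not demonstrate.

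The redundancy itself rests only on the ordinary meaning of the two terms. That it reflects an error is an inference, to be confirmed from the full protocol and CRF. The documents do not show which limit or label is right, and no view is taken on that here.

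**What to change.** 1. Compare both lines with the full protocol and the CRF.
2. Have the sponsor decide which cell count each limit is meant for, and reword the two lines so that each limit is tied to a named count and each can act.
3. If the operational documents carry the same wording, amend them, notify the centres, and check patients already enrolled against the corrected text.
4. If the operational documents are already coherent, publish a correction to the article; nothing further is needed at the centres.

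The cost is small: a one-line correction in either case. If an amendment is needed, add a notice to the centres and a check of baseline counts for enrolled patients. Sample size and analysis are unaffected.

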#### CGA

As mentioned before, due to the specialty of elderly population, enrolled patients will receive a comprehensive assessment called CGA (including social support, general status, body function, nutritional status, mental health, cognitive ability and so forth) both before and after treatment. Detailed procedures of CGA are listed in Table 1.

**Table 1 Tab1:** Domains and measures accessed by CGA before and after treatment

Domain with measure	No. of items	Range of score
Quality of life and specific module for EC		
EORTC QLQ-C30 (Version 3.0) [34]	30	30–126
QLQ-OES-18 [35]	18	18–72
Functional status		
ECOG performance status [36]		0–5
Karnofsky performance status [37]		0–100
Activities of daily life (Barthel index) [38]	10	0–100
Instrumental activities of daily life (Lawton’s) [39]	8	0–5/8
Comorbidity		
Charlson comorbidity index [40]	19	0–37
Cognitive status		
Mini Mental State Examination [41]	11	0–30
Psychological status		
Geriatric depression scale-5 items [42]	5	0–5
Nutritional status		
Body mass index [43]		
Mini-nutritional assessment [44]	18	0–100
Social support		
Medical Outcomes Study - social support survey [45]	20	20–100

*CGA* comprehensive geriatric assessment, *EC* esophageal cancer, *ECOG* Eastern Cooperative Oncology Group, *EORTC* The European Organization for Research and Treatment of Cancer, *MOS* Medical outcomes study

### Radiotherapy

For patients with lower-thoracic EC or EGJC, a series of pre-treatment procedure will be adopted to minimize the effect of stomach-volume-variation during treatment delivery. Patients should be fasted for at least 4 h and then drink 200-300 ml semiliquid 15 min before CT simulation and daily irradiation. Supine position is performed with both arms straight beside the body. Head and neck hood is recommended for patients with cervical or upper-thoracic EC, while body film is used for middle, lower-thoracic EC and EGJC.

The Gross Tumor Volume (GTV-T) is defined as the primary tumor. The GTV-T will be determined using all available resources (physical examination, upper gastrointestinal contrast, endoscopy, EUS, CT-thorax/abdomen, MRI-thorax/abdomen, PET-CT, etc.).

The metastatic regional nodes (GTV-N) is defined as any lymph node diagnosed as or highly-suspected as metastatic.

As for the contouring of Clinical Target Volume (CTV), Involved-field radiotherapy (IFRT) is adopted. CTV consists of GTV-T plus a 0.6 to 0.8 cm circumferential margin, a 3 cm craniocaudal margin and GTV-N plus a 0.5 cm margin in all directions. For patients whose highest/lowest metastatic lymph nodes not exceeding 3 cm from the primary tumor, the upper/lower border of the is 3 cm superior/inferior to the primary tumor. For patients whose highest/lowest metastatic lymph nodes exceeding 3 cm from primary tumor, the upper/lower boundary of CTV is 0.5 cm superior/inferior to the furthest metastatic lymph node. No prophylactic irradiation is given to lymph node drainage regions. The PGTV is created by expanding GTV-T by 1.0 cm craniocaudally and 0.5 cm radially and GTV-N by a uniform 0.5 cm margin, and the PTV is derived from CTV plus a uniform 0.5 cm margin. The typical contouring of targets for tumor in different locations are depicted in Fig. 2 respectively.

**Fig. 2 Fig2:**
[figure not shown]
Targets contouring of (**a**) upper thoracic esophagus (Ut); (**b**) middle thoracic esophagus (Mt); (**c**) lower thoracic esophagus (Lt). Red area indicates GTV-T, grey area includes GTV-N, blue area outlines PGTV and green area outlines PTV

The radiotherapy technique of SIB is performed 5 times a week. For thoracic esophagus, prescription dose is 95% PTV/PGTV 50.40Gy/59.92Gy/28f. For EGJC, prescription dose is 95% PTV/ PGTV 45.0Gy/53.5Gy/25f.

Both lungs, heart, spinal cord and spinal cord PRV should be contoured on the simulation images. For tumor of lower-thoracic EC and EGJC, physicians should also delineate stomach, liver, both kidneys and bowels (including small intestine and colon) as OARs. Bowels and spinal cord should be contoured 2 cm superior and inferior to PTV. OARs such as lungs, heart, stomach, kidneys and liver should be delineated from their upper border to their lower end. The volume of lung tissue receiving 20Gy or more should not exceed 28% of the total lung volume (V20 **<** 28%). The mean dose of lung tissue should be lower than 16Gy (Dmean lung **<**16Gy). Other dose constraints to OARs include: V40 heart **<** 30%, V30 heart **<** 40%, V40 stomach **<** 40%, Dmax stomach **<** 55-60Gy, V40 small intestine **<** 40%, Dmax small intestine **<**55Gy, V30 liver **<** 30%, V20 kidney **<** 30% and Dmax spinal cord PRV **<** 45Gy.

### Chemotherapy

S-1 will be orally taken twice daily (or through nasal feeding tube for patients with enteral nutrition) within half an hour after meals during treatment days. It should not be taken during weekends or whenever radiotherapy is interrupted or stopped. The specific dosage for each patient is calculated according to body surface area in Table 2:

**Table 2 Tab2:** Relationship between body surface area and dose of S-1

Body surface area (m^2^)	Initial dose
<1.25	40 mg, bid
≥1.25~<1.50	50 mg, bid
≥1.5	60 mg, bid

Generally, 4–8 weeks are needed for patients to recover after completion of SIB + S-1 (status of food intake, physical capacity, biochemical tests, etc.). Four cycles of S-1 will be given to those eligible for consolidation chemotherapy. Treatment schedule for patients in both arms is shown in Fig. 3. The daily-dose of consolidated S-1 is the same as that of concurrent phase, but it will be administered for the first 2 weeks on each 21-days cycle. Blood routine should be monitored every week and hepatic and renal functions every cycle during chemotherapy.

**Fig. 3 Fig3:**
[figure not shown]
Treatment schedule for both arms CCRT: Concurrent Chemoradiotherapy; RT: Radiotherapy

### Toxicity and adverse events

All treatment-related toxicities and adverse events should be graded according to the toxicity criteria of the Radiation Therapy Oncology Group (RTOG) and Common Terminology Criteria of Adverse Events (CTCAE) version 4.0 and recorded on patients’ case report form (CRF) in detail. Serious Adverse Events (SAE) should be reported to the institutional ethical review committee in 24 h and dealt with properly.

S-1 should be terminated in case of Grade 2 anemia, thrombocytopenia, hepatic or renal dysfunction, Grade 4 leukopenia/neutropenia, Grade 3 radiation esophagitis and other non-homological Grade 3 toxicities. If adverse events de-grade to Grade 0–1 within 1 week of drug withdrawal, patient can re-take S-1 at original dose, otherwise chemotherapy should be stopped henceforward. If Grade 3/4 radiation pneumonitis developed, both radiotherapy and oral intake of S-1 should be terminated. Consolidation of S-1 will be re-assessed within 4–8 weeks after radiotherapy whichever grade of toxicities developed during dCRT.

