### Follow-up

Tumor regression should be evaluated according to RECIST Version 1.1 within 1–2 month after completion of treatment and rates of cCR and cPR should be documented. All patients should be followed up for at least 5 years after completion of the protocol and the time interval is every 3 months for the first 2 years, every 6 months for 3–5 years and once a year after 5 years.

Every follow-up should include: a. History-taking: symptoms of cough, fever, hoarseness, dysphagia or chest tightness, etc. b. Blood routine, basic metabolic panel, tumor markers, etc. c. Contrast enhanced CT of neck, thorax and abdomen, ultrasound of neck and abdomen, upper gastrointestinal contrast, bone scan (in case of bone pain or abnormally-elevated alkaline phosphatase), CT or MRI of brain (in case of any symptoms related to central nervous system), etc. d. Documentation of patients’ status of survival, disease progression, subsequent treatment, nutrition, life quality and late toxic effects, etc.

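### The adverse event recording rule reads most naturally as limited to treatment-related events; in this open trial, with arms of unequal planned length, the toxicity comparison can be biased by an unknown amount

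*Protocol article*

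**What the plan says.** All references are to the protocol article.

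- **Recording rule** (Toxicity and adverse events). The rule opens with these words: "All treatment-related toxicities and adverse events should be graded according to the toxicity criteria of the Radiation Therapy Oncology Group (RTOG". It also names CTCAE version 4.0, and it wants the result "recorded on patients’ case report form (CRF) in detail". The same sentence applies to both arms.
- **Serious events** (same section): "Serious Adverse Events (SAE) should be reported to the institutional ethical review committee in 24 h and dealt with properly". No relation to treatment is required here.
- **Blinding** (Study design and objectives): "This study is an open, multicenter Phase III clinical trial". About 15 centres take part, and under Quality assurance each centre's own physician enters its CRF data.
- **Role of toxicity** (Study design and objectives): "Secondary objectives include progression-free survival, recurrence-free survival (local-regional and distant), disease failure pattern, toxicity profile as well as quality of life".
- **Length of treatment** (Radiotherapy; Chemotherapy): 28 fractions, or 25 for junctional tumours, at five per week in both arms. In the S-1 arm, "Generally, 4–8 weeks are needed for patients to recover after completion of SIB + S-1", after which "Four cycles of S-1 will be given to those eligible for consolidation chemotherapy". Each cycle lasts 21 days, with S-1 taken in the first two weeks.
- **Laboratory checks** (Chemotherapy): weekly blood counts, and liver and kidney tests each cycle, are specified for the time on chemotherapy.
- **Follow-up, both arms**: visits every three months for two years, with symptom history, blood tests and "Documentation of patients’ status of survival, disease progression, subsequent treatment, nutrition, life quality and late toxic effects, etc".

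**The concern.** If relation to treatment is the condition for entering an event, the dataset depends on a judgement made by physicians who know the arm. The two arms also differ in what an event can be blamed on. Once radiotherapy has ended, a SIB patient is off treatment. An S-1 patient in consolidation is taking a drug. Anaemia, poor appetite, infection or abnormal liver tests in that period can be put down to the drug in one arm, and to the tumour or to age in the other. The S-1 patient is also tested more often under the stated schedule, so laboratory abnormalities are more likely to be found.

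The Background section argues for S-1 partly on keeping toxicity low in elderly patients, so the size of any excess toxicity matters to how the result is used. A filter applied when data are entered cannot be fully undone later, because non-serious events that were never graded on the CRF are not there to analyse.

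**Working it through.** The plan states no figure for this point, so there is none to reproduce. The check has three parts.

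**1. What the sentence permits.** Two readings are possible:

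- (a) *Treatment-related* governs both *toxicities* and *adverse events*, so unrelated events need not be entered.
- (b) It governs *toxicities* alone, so all adverse events are entered.

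Reading (a) is the more natural. Under (b), naming treatment-related toxicities separately would be redundant, since they are already adverse events. If sites differ in their reading, about 15 centres may be working to two rules.

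**2. How the arms differ in time.**

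- Radiotherapy, both arms: 28 / 5 = 5.6 weeks (junctional tumours 25 / 5 = 5 weeks).
- Consolidation cycles: 4 × 3 = 12 weeks, of which 4 × 2 = 8 weeks are dosed.
- End of radiotherapy to end of cycle 4: 4 + 12 = 16 to 8 + 12 = 20 calendar weeks.
- Of these 16 to 20 weeks, 4 to 8 are recovery without S-1. All of this applies only to patients eligible for consolidation.

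**3. Illustration of size.** Let *p* be the proportion of patients with a background event (one that would occur in either arm) during the cycle weeks, and let *a* be the share of such events attributed to treatment. If every S-1 patient has all four cycles, then

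spurious risk difference = p × (a in S-1 arm − a in SIB arm).

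The documents give neither *p* nor *a*. I assume a constant background rate of 2% to 5% per month over the 12 cycle weeks, and no attribution to treatment in the SIB arm. Twelve weeks is 12 / 4.348 = 2.76 months.

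- 2% per month: p = 1 − exp(−0.02 × 2.76) = 5.4%
- 5% per month: p = 1 − exp(−0.05 × 2.76) = 12.9%

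| Share attributed in S-1 arm | 2% per month | 5% per month |
|---|---|---|
| 25% | 1.3 points | 3.2 points |
| 50% | 2.7 points | 6.4 points |
| 100% | 5.4 points | 12.9 points |

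The difference shrinks in proportion if fewer S-1 patients have consolidation, or if some SIB-arm events are attributed to earlier radiotherapy. If all events are recorded in both arms whatever their cause, this component is zero by construction. Unequal laboratory testing is a separate source and is not in the table.

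**The case against.** The case against has real weight.

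- **The rule does not say *only*.** A reader might infer that unrelated events are barred from the CRF. The text does not say so, and reading (b) removes the attribution problem. This stands as a limit on the claim. It does not clear the sentence, which should not leave the choice to each site.
- **This is a journal article.** An adverse event window and causality procedure may well be in the full protocol or CRF, which are not shown, and their absence is no fault. The point here is different: a recording rule is stated, and its wording ties recording to cause.
- **Exposure is easily overstated.** A reader might infer that S-1 patients are on treatment 16 to 20 weeks longer. They are not: the gap is drug-free, dosing takes 8 weeks, and only eligible patients are treated.
- **The direction is not shown.** A reader might infer that the comparison is biased against S-1. Investigators who share the Discussion's view of S-1 as a drug of low toxicity could under-attribute events to it, and SIB-arm events can still be attributed to radiotherapy. Extra toxicity that S-1 truly causes is an effect of the strategy, not bias.
- **The size cannot be taken from the survival assumption.** The assumed 65% one-year survival gives a hazard of −ln(0.65) / 12 = 0.036 per month. It is tempting to use this as a background event rate, but it is a death rate, and nothing in the documents links it to the frequency of severe adverse events.
- **Other data are collected.** Three-monthly bloods, symptom history, nutrition and quality of life in both arms, together with serious event reports that need no attribution, would recover part of what is lost. They do not amount to graded all-cause events: the visits are three months apart, late toxic effects again need a judgement of cause, and the stated route for serious events is the ethics committee.

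**Conclusion.** The point holds in a limited form. The recording sentence most naturally makes relation to treatment a condition for CRF entry. In an open trial with arms of unequal planned length, and with laboratory checks specified for chemotherapy only, both attribution and detection can differ by arm. The comparison of toxicity can therefore be biased, most plausibly but not certainly against S-1.

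The size is unknown. The figure of about 3 to 6 points rests on assumptions: 2-5% per month, 12 cycle weeks, consolidation completed by all, half of events attributed to S-1 in one arm and none to treatment in the other. It shows that the effect need not be trivial; it is not an estimate. The primary endpoint, overall survival, is not affected. The change is worth making because a secondary objective is at stake and events not recorded are hard to recover.

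**What to change.** 1. Reword the sentence under Toxicity and adverse events so that every adverse event, regardless of presumed cause, is graded and recorded on the CRF in both arms. Recording should run from randomisation over one common window that covers the longest planned S-1 course. From the start of radiotherapy that course is 5.6 + 8 + 12 = 25.6 weeks; about 30 weeks from randomisation would leave some allowance for time to start and for delays.
2. Make the all-cause incidence of grade 3 or higher events in that window the between-arm toxicity comparison. Genuine S-1 toxicity is still counted, and the result no longer depends on attribution in either direction.
3. Keep the investigator's attribution as a separate CRF field for a supporting analysis.
4. Because laboratory monitoring differs by arm as written, interpret laboratory-based events with that in mind, or compare them at the follow-up visits common to both arms.

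The cost is a wording change, one CRF field, more event entry for sites and higher event counts in both arms. No extra patients or visits are needed. If the full protocol already requires all-cause recording, only the article's sentence needs clarifying.
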